#### Intervention Description

CSEs were designed to improve the endurance of core muscles that stabilise the trunk and pelvis. The CSEs program consists of 23 exercises focused on trunk muscle strengthening, proprioception, selective movements of the trunk and pelvis muscle and coordination. They are carried out in the supine position, sitting on a stable surface and on an unstable surface (physioball). The exercises involve changes in the position of the body with or without resistance. Training is determined by the patient’s ability to perform easy exercises and their progress to more challenging exercises. Adequate rest periods are allowed between exercises. Start with simple movements and progress to multi-plane movements when the basics are secure. For each exercise, ten repetitions are performed, two of them with the eyes closed. If the patient is afraid in sitting exercises on a physioball, they should not be forced to close them. It is not necessary that the patient perform all exercises per session. It may be performed depending on the patient’s possibilities, but most important is that they were performed 30 min of CSEs, and were recorded. For monitoring the perceived individual’s exertion of CSE training, the Borg scale of perceived exertion will be used [50]. The intensity of the effort perceived by the patient during training will remain moderate (4–5 points-score). They would not move on to higher levels until they had mastered the exercise they were engaged in. The physiotherapists perform the therapy with their hands on the patient to ensure proper quality of movement, and do not participate in the patient’s evaluation. When the patient performs them correctly, they will perform them again alone (see Figure 1).

Transcutaneous electrical nerve stimulation (TENS). The high frequency of TENS is 100 Hz; 0.2 µs pulse width, mm-diameter electrodes placed on the skin over the lumbar erector spinae muscles (3 cm lateral to the L3 and L5 spinous process). The intensity of stimulation is twice the sensory threshold (the minimum intensity the subject could feel), which was barely below the motor threshold. The pulse trains were delivered with a two-channel stimulation device (Cefar PRIMO PRO, tens. 2 channels).

The comparator of EG is CP. CP involves different interventions improving functional capacity and reducing disability. The common feature of CP is that it consists of a treatment performed by the physiotherapist according to the degree of affectation of the particular patient, and according to the degree of accomplishment of the objectives set. CP may consist in a variety (or combination) of multiple components such as tone normalisation based on hands-on therapy interventions with sensory feedback by manual contact [51], passive or active joint mobilisation for maintaining range of motion, and active or active-assisted exercise of affected side [52], as well as sit to stand training [53] with or without gripping on wall bars, sitting balance (without core stability exercises), standing balance training [54] and gait re-education (walking between parallel bars or with a physiotherapist). 

Co-interventions: during the five-week intervention phase, patients can receive other usual types of rehabilitation management (such as occupational therapy, speech therapy and neuropsychology) in accordance with local practices. All these co-interventions are being recorded, and measures will be taken to control for possible performance bias. Interventions normally last 30–45 min. In this phase of the stroke, the patient is usually highly motivated to recover and especially regain balance in sitting, standing and walking, and thus be able to perform their ADLs. It is very unlikely that the treatment cannot be carried out. This could only be the case for patients with a cognitive impairment, but these are initially excluded from the study. 

### 2.6. Participant Timeline

The study has five assessments: T0 (baseline), T1 (week three, only primary outcomes), T2 (week five, end-point, 25 sessions), T3 (week 17) and T4 (week 29). Study duration per patient: 29 weeks (See Figure 2).

### 2.7. Outcomes Measures

Primary outcome measures include: Dynamic sitting balance and coordination measured by S-TIS 2.0 [48]. This scale is a Spanish version of the Trunk Impairment Scale version 2.0 [55]. This scale aims to evaluate the trunk in patients who have suffered a stroke. The dynamic subscale contains items on the lateral flexion of the trunk and unilateral lifting of the hip. To assess the coordination of the trunk, the individual is asked to rotate the upper or lower part of his or her trunk six times, initiating the movements either from the shoulder girdle or from the pelvic girdle, respectively. There are two subscales; the first one has 10 items and the second one has six. The highest possible total score is consequently 16 points, which indicates an optimal dynamic sitting balance and sitting coordination. If the patient cannot maintain a sitting position for 10 s without back and arm support, with hands on thighs, feet in contact with the ground and knees bent at 90° (starting position), the total score for the scale is 0 points. This scale is utilised for inclusion criteria, and at T0, T1, T2, T3 and T4.Gait by stepping section of Brunel Balance Assessment (BBA) [56]. It is designed to assess functional balance for people with a wide range of abilities, and has been tested specifically for use post-stroke. There are three sections to the assessment: sitting, standing and stepping. In this study, only the stepping section is utilised. It consists of six levels to assess standing functional balance and a 5-m walk. At each level, the patient receives a score for his/her efforts. This gives an indication on whether the patient is improving within a level, even if he/she is not able to progress to the next level. The score also reflects how well the individual is functioning within that stepping section. The higher score is six points, and the individual is able to walk 5 m independently. Stepping is evaluated at T0, T1, T2, T3 and T4.

Secondary outcome measures include: Sitting functional balance is assessed by the Spanish version of Function in Sitting test (S-FIST) [57]. It is a bedside evaluation of sitting balance and functional sitting everyday activities that assess sensory, motor, proactive, reactive and steady balance factors. The S-FIST consists of 14 tested parameters with an ordinal scale (0–4) for each test item, with 0 indicating the lowest level of function and 4 the highest level. Each participant sat at the edge of a standard hospital bed without air mattresses, with the proximal thigh (1/2 femur length) supported by the bed. The bed height was adjusted and a step stool was used if necessary to bring the hips and knees to approximately 90° flexion, with both feet flat on the floor or stool. The higher score is 56 points. Sitting functional balance is evaluated at T0, T2, T3 and T4.Standing balance and risk of falling is evaluated by Berg Balance Scale (BBS) [58,59]. It provides a psychometrically sound measure of balance impairment. It is used objectively determine a patient’s ability (or inability) to safely balance during a series of predetermined tasks. It is a 14-item scale; patients must maintain positions and complete moving tasks of varying difficulty. In most items, patients must maintain a given position for a specified time. Each item consists of a 5-point ordinal scale ranging from 0 to 4, with 0 indicating the lowest level of function and 4 the highest. A score of 56 indicates functional balance. A score of < 45 indicates that individuals may be at greater risk of falling. BBS is assessed at T0, T2, T3 and T4.Postural control is evaluated by the Spanish version of Postural Assessment Scale for Stroke (S-PASS) [60]. It was designed specifically for patients with a stroke, regardless of postural competence. It has two subscales: mobility and balance. The first measures the patient’s ability to change position from lying, sitting and standing, and the second in maintaining stable postures in sitting and standing. The S-PASS consists of 12 items with a 4-point scale, where items are scored from 0–3. The higher score is 36 points, indicating an optimal postural control. It is evaluated at T0, T2, T3 and T4.Lower limb spasticity by Modified Ashworth Scale (MAS) [61]. This tool measures resistance during passive soft-tissue stretching of muscle. It is performed while the assessor moves the hip adductors, knee extensors and ankle plantar flexors in the supine and lateral position. The MAS is assessed at T0, T2, T3 and T4.ADL by Barthel Index (BI) [62]. This shows the degree of independence of a patient from any assistance. It covers 10 domains of function (activities): bowel and bladder control, as well as help with grooming, toilet use, feeding, transfers, walking, dressing, climbing stairs and bathing. The ADL is evaluated at T0, T2, T3 and T4.Health-related quality of life is measured by the Spanish-version of 5-Dimensions Questionnaire (EQ-5D-5L) [63,64]. It is a generic patient’s health-related quality of life measurement with evidence of good reliability and validity in various disease populations, including strokes. Patients chose five levels of severity (1, no problem; 2, slight problem; 3, moderate problem; 4, severe problem; and 5, unable to function/extreme problem) in five dimensions (mobility, self-care, usual activity, pain/discomfort and depression/anxiety), and rated their overall health status via the EQ-VAS. Quality of life is assessed at T0, T2, T3 and T4.Rate of falls is measured by a specific registry created specifically for this study. The outcome is defined as the average number of falls per patient during the intervention period and follow-up. It is recorded at T0 (falls before stroke), T2, T3 and T4.Gait speed is assessed by BTS G-Walk. It is a wireless system consisting of an inertial sensor composed by a triaxial accelerometer, a magnetic sensor and a triaxial gyroscope that was positioned on S1 vertebrae. From the data acquired, the system extrapolates all spatial-temporal gait. The patient walks for one minute without being aided; this variable is only performed if the patient has a 6-point stepping section of BBA.

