### 2.8. Statistical Analysis

The main analysis population will be defined by intention-to-treat, comprising all randomised participants with a baseline assessment, regardless of later events such as protocol violations, missing data or loss to follow-up. Missing data will be imputed and the impacts of imputation on results will be explored. Secondary analyses will be conducted, restricted to the population of participants who followed the study protocol and had no missing data.

General linear models with repeated measures design will be used to test the effect of the Core Stability program (with or without TENS) on the change in the outcome of interest (total S-TIS 2.0 score or any other outcome) between the baseline and follow up (five weeks), using a repeated measures design with two levels (baseline, five weeks), as well as a two-level factor testing the intervention (usual care). The models will adjust for clinically relevant covariates, such as site, age, baseline levels of the dependent outcomes or severity of stroke. Similar models will be built to explore the effect of Core Stability at different time points (three months; six months). Similar models will test the effect of TENS added to Core Stability on primary and secondary outcomes, as well as primary and secondary endpoints.

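### Falls are not exempted from the change-from-baseline linear model, although their only baseline value is a pre-stroke count over an unstated period

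*Protocol article*

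**What the plan says.** The last paragraph of the Introduction names fall rate among the secondary objectives. Section 2.7 (Outcomes Measures) takes falls from a study-specific registry and defines the measure: "The outcome is defined as the average number of falls per patient during the intervention period and follow-up". The next sentence gives the time points: "It is recorded at T0 (falls before stroke), T2, T3 and T4". It does not say how far back the pre-stroke count reaches.

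Section 2.8 (Statistical Analysis) sets one model for all outcomes. It is a general linear model that tests the effect of the programme "on the change in the outcome of interest (total S-TIS 2.0 score or any other outcome"), "using a repeated measures design with two levels (baseline, five weeks"). For later visits, "Similar models will be built to explore the effect of Core Stability at different time points (three months; six months"). Covariates are described as clinically relevant ones, "such as site, age, baseline levels of the dependent outcomes or severity of stroke". No count model, exposure term or exception is given for falls.

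Section 2.6 (Participant Timeline) places the visits at "T2 (week five, end-point, 25 sessions), T3 (week 17) and T4 (week 29"). Section 2.2 (Recruitment) expects 10% loss to follow-up.

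**The concern.** Put together, sections 2.7 and 2.8 make the falls response a difference between two things that are not the same variable.

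- **Health state.** Patients enter within 30 days of a first stroke (section 2.4), so the T0 count describes life before the disease under study. For S-TIS 2.0 or the Berg scale, T0 is the same scale measured after the stroke.
- **Time window.** The T0 window is unstated. The windows after it are 5, 12 (17 − 5) and 12 (29 − 17) weeks. A difference of raw counts over unequal windows moves with the windows as well as with falls.
- **Mismatch with the definition.** Section 2.7 defines an outcome over the intervention and follow-up. The main model in section 2.8 tests change up to week 5.
- **Denominator.** The outcome is called a rate but is a mean count per patient. A patient observed for less time has fewer recorded falls for that reason alone.

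At stake are the interpretability and precision of the falls result.

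**Working it through.** **The plan's own figure.** No figure is given for falls. The only sample-size figure, for S-TIS 2.0, reproduces: 2 × (1.96 + 0.8416)² × 4² / 1.6² = 98.1, rounded up to 99 per group, and 99 / 0.9 = 110. The falls issue does not touch it.

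**Assumptions, none from the document.** Control rate after stroke 2 falls per person-year; rate ratio 0.5; negative binomial dispersion k = 1; pre-stroke rate 0.5 or 1.0 per year over a look-back of 26 or 52 weeks; correlation of 0.3 between a patient's pre- and post-stroke frailty; 110 per arm; 10% of patients observed for only part of the window. The 29-week response is taken as the cumulative count from randomisation, because section 2.8 does not say how falls at T4 are counted.

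**Hand calculation: five weeks, pre-stroke rate 0.5 per year over 52 weeks, no early leavers.** A count with mean m has variance m + k·m².

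- Control mean 2 × 5/52 = 0.192, variance 0.229. Experimental mean 0.096, variance 0.105. Difference 0.096.
- Pre-stroke mean 0.5, variance 0.5 + 0.25 = 0.75. Covariance with post-stroke falls 0.3 × 0.192 × 0.5 = 0.029 (control) and 0.3 × 0.096 × 0.5 = 0.014 (experimental).
- Variance of change: 0.229 + 0.75 − 2 × 0.029 = 0.92 (control); 0.105 + 0.75 − 2 × 0.014 = 0.83 (experimental).
- Follow-up falls only: SE = √((0.229 + 0.105)/110) = 0.055, z = 1.74, power about 41%.
- Change from T0: SE = √((0.92 + 0.83)/110) = 0.126, z = 0.76, power about 12%.

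Subtracting T0 therefore multiplies the variance by about 5 (1.75 / 0.334) in this scenario.

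**Simulation with early leavers, 600 trials per row, rate ratio 0.5 (power, %).** Monte Carlo error is about 2 points.

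| Window | Pre-stroke rate, look-back | Change from T0 | Linear, adjusted for T0 | Follow-up falls only | Negative binomial, exposure offset |
|---|---|---|---|---|---|
| 5 wk | 0.5/yr, 52 wk | 10.3 | 38.3 | 38.7 | 37.2 |
| 5 wk | 1.0/yr, 52 wk | 8.5 | 39.0 | 38.7 | 37.5 |
| 5 wk | 0.5/yr, 26 wk | 16.5 | 41.3 | 42.0 | 39.5 |
| 29 wk | 0.5/yr, 52 wk | 79.5 | 91.7 | 91.0 | 92.2 |
| 29 wk | 1.0/yr, 52 wk | 59.8 | 90.2 | 90.3 | 91.0 |
| 29 wk | 0.5/yr, 26 wk | 85.3 | 90.5 | 90.0 | 91.0 |

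At a rate ratio of 1.0, rejection was about 4% to 6% for every method.

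**Lower rate: 1.5 falls per person-year, 99 per arm (110 × 0.9).** At rate ratio 0.5, five-week power was 8% with the subtraction against 22–30% without, and 29-week power 67% against 76–80%. At rate ratio 0.6 the figures were 9% against 13–16%, and 59% against 61–69%.

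**Bias.** At rate ratio 0.5 and five weeks, the mean between-arm difference in change was −0.09 to −0.10, as in the adjusted model. At 29 weeks it was about −0.53 in both. The full-exposure value there is −0.558. The gap comes from early leavers: average exposure is 0.9 + 0.1 × 0.55 = 0.955, and 0.558 × 0.955 = 0.533. With equal loss in both arms, the missing denominator costs about 4.5%.

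**Within-arm change.** In the higher-rate simulations the control-arm mean change ran from −0.81 to −0.07 falls at five weeks and from +0.06 to +0.81 at 29 weeks. Only the assumed pre-stroke rate and look-back were varied, so neither the sign nor the size describes recovery.

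**Effect of the covariate.** If Y is follow-up falls, X pre-stroke falls and A the arm, then Y − X = a + b·A + c·X + e is the same model as Y = a + b·A + (c + 1)·X + e. The coefficient b is identical, so adjusting for T0 undoes the subtraction.

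**The case against.** The strongest reply is that section 2.8 already mentions baseline levels of the outcome as a covariate, and that with this adjustment the power loss disappears. The algebra is right. But the list is introduced as examples and joined by an *or*, so it does not commit the analyst to adjust falls for T0. The five-week versus full-period mismatch and the missing exposure term would also remain.

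A second reply is that models at three and six months are planned, so week 5 is not the only look at falls, and that missing data are to be imputed. Both are true. The later models keep the same change-from-baseline form, and the imputation sentence does not say how partly observed fall counts are treated. Still, no difference in loss between arms is shown, so bias from early leaving is only a possibility.

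Some stronger readings are tempting but unsupported:

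- A reader might infer that the falls comparison is biased or that a real effect would be hidden. Pre-stroke falls precede randomisation and balance in expectation, so the contrast is noisier and remains valid.
- A reader might set a five-week change score against a 29-week count model and credit the whole gap to method. Much of that gap is window length; only same-window comparisons are fair.
- A reader might infer that a normal model for counts is itself costly. Within each window the negative binomial model was within about 2 points of the adjusted linear one. Its advantage is the exposure term and a rate ratio.
- A reader might extend the point to the ordinal scales. Their T0 value is measured after the stroke on the same scale, so this defect does not apply to them.

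**Conclusion.** The point holds as a conflict between a stated rule and a stated outcome. Section 2.8 covers every outcome with a change-from-baseline model, and section 2.7 supplies for falls a baseline that cannot be meaningfully subtracted. Because the model is named and falls are not exempted, this is more than detail left to an analysis plan.

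The cost is lost precision and an uninterpretable within-arm change. Over the scenarios with rate ratio 0.5, five-week power is about 8–17% with the subtraction against roughly 22–42% without, and 29-week power about 60–85% against 76–92%. These ranges pool different assumed rates, so the row-by-row comparison is the one to read. The loss is large at five weeks and grows with the pre-stroke count; at 29 weeks it is smaller and in some scenarios slight. Every fall rate, dispersion and effect is an assumption. The point affects one secondary outcome and leaves the primary outcomes and the sample size alone. It should be corrected, but it does not threaten the trial's main conclusion.

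**What to change.** State in the analysis plan, before unblinding, that falls are exempt from the change-from-baseline model. Then:

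1. Analyse falls after randomisation over the intervention and follow-up, per person-time. One suitable model is negative binomial regression with log time at risk as offset, reporting a rate ratio with its confidence interval.
2. Use pre-stroke falls only as a covariate, and state the look-back period they cover.
3. Report the five-week window as a sensitivity analysis.

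The cost is mainly wording. The analysis needs each patient's time under observation, which the article does not expressly say is recorded, so the team should confirm that visit and withdrawal dates are available. If the look-back was not standardised when the T0 count was collected, that should be reported as a limitation of the covariate.

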## Abstract

Background: Trunk impairment produces disorders of motor control, balance and gait. Core stability exercises (CSE) are a good strategy to improve local strength of trunk, balance and gait. Methods and analysis: This is a single-blind multicenter randomized controlled trial. Two parallel groups are compared, and both perform the same type of therapy. A control group (CG) (*n* = 110) performs conventional physiotherapy (CP) (1 h per session) focused on improving balance. An experimental group (EG) (*n* = 110) performs CSE (30 min) in addition to CP (30 min) (1 h/session in total). EG is divided in two subgroups, in which only half of patients (*n* = 55) perform CSE plus transcutaneous electrical nerve stimulation (TENS). Primary outcome measures are dynamic sitting, assessed by a Spanish version of Trunk Impairment Scale and stepping, assessed by Brunel Balance Assessment. Secondary outcomes are postural control, assessed by Postural Assessment Scale for Stroke patients; standing balance and risk of fall assessed by Berg Balance Scale; gait speed by BTS G-Walk (accelerometer); rate of falls, lower-limb spasticity by Modified Ashworth Scale; activities of daily living by Barthel Index; and quality of life by EQ-5D-5L. These are evaluated at baseline (T0), at three weeks (T1), at five weeks (end of the intervention) (T2), at 17 weeks (T3) and at 29 weeks (T4). Study duration per patient is 29 weeks (a five-week intervention, followed by a 24-week post-intervention).

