The primary objective of this study is to evaluate the effectiveness of CSEs protocol (with and without TENS), in addition to conventional physiotherapy (CP) to improve dynamic sitting balance and gait (stepping) at short/mid-term in the subacute phase of a stroke. Secondary objectives are to evaluate the effectiveness of CSEs (with and without TENS) in addition to CP to improve postural control, standing balance, fall rate, risk of falls, gait speed, lower limb spasticity, ADL and QoL. Another secondary objective is to explore the sustainability of the effects of CSEs over time. It is important to know whether the treatment effects are sustainable over time, or if continuous therapeutic input is necessary to maintain the level of function even after being discharged (home).

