A decrease in gait velocity and double support time could represent an attempt at increasing postural stability to reduce fall risk [69]. Specifically, decreased velocity may reduce the body’s momentum, increasing the likelihood of recovering from a loss of balance. A walking speed of 0.8 m/s is predictive of weak functional abilities, while a speed of 0.6 m/s establishes a threshold below which the risk of falling is critical [77]—the minimally clinically important difference in stroke patients (0.6; 0.8 m/s) [78]. 

One of the first objectives of rehabilitation in the subacute phase of the stroke is to achieve optimal trunk control and dynamic balance while sitting. The proposal of this study is to achieve this by training the core muscles. This results in a better balance in sitting, standing, and in a more efficient gait [79]. The earlier these patients can be autonomous, the less time they will be inactive [80], and in this way the adverse effects of immobilisation can be reduced [81]. Additional trunk rehabilitation is beneficial in improving gait performance in sub-acute stroke [82]. Therefore, if the results of this study are positive, we recommend to incorporate these exercises as early as possible in a stroke rehabilitation program. 

Another important goal of this study is to discover whether the treatment effects are sustainable over time, or if the continuous therapeutic input is necessary to maintain the level of function even after the discharge home [83]. In our knowledge, there is no systematic review about the long-term effects of core stability exercises on improving balance and gait in a stroke subacute phase.

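### Gait speed is measured only at BBA stepping 6, a primary outcome the programme is meant to change, and the general analysis rule does not work for it

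*Protocol article*

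**What the plan says.** Protocol article, section 1 (Introduction): the secondary objectives include showing that the programme is effective "to improve postural control, standing balance, fall rate, risk of falls, gait speed, lower limb spasticity, ADL and QoL". Gait speed is thus an outcome on which the groups are to be compared.

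Section 2.7 (Outcomes Measures): gait speed comes from a one-minute unaided walk with a body-worn sensor, and "this variable is only performed if the patient has a 6-point stepping section of BBA". Six is the top of that section: "The higher score is six points, and the individual is able to walk 5 m independently". No exception is made for any visit.

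Stepping is itself a primary outcome. The Abstract states: "Primary outcome measures are dynamic sitting, assessed by a Spanish version of Trunk Impairment Scale and stepping, assessed by Brunel Balance Assessment". It is scored before and after treatment: "Stepping is evaluated at T0, T1, T2, T3 and T4". The primary objective is "to improve dynamic sitting balance and gait (stepping) at short/mid-term in the subacute phase of a stroke".

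Section 2.8 (Statistical Analysis) sets one approach for the total S-TIS 2.0 score and for every other outcome: a repeated-measures linear model with two levels, baseline and five weeks, in all randomised patients who have a baseline assessment. It adds: "Missing data will be imputed and the impacts of imputation on results will be explored". The only other population named is protocol followers without missing data.

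Section 3 (Discussion) takes 0.8 and 0.6 m/s as absolute walking speeds that mark weak function and critical fall risk, and then calls the same two figures "the minimally clinically important difference in stroke patients (0.6; 0.8 m/s)".

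**The concern.** Whether a patient has a speed at five weeks depends on the stepping score at five weeks. The trial's own hypothesis is that treatment changes that score. If it does, the measured patients in the experimental group include some who would not have been measured under control treatment, and these are likely to be the slower ones. The two measured sets are then no longer the groups that randomisation created.

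The general rule in section 2.8 leaves no sound route for this outcome. A change model needs a baseline speed, which exists only for patients already at stepping 6 although they entered with S-TIS 2.0 of 10 or less, within 30 days of stroke. Imputation across the intention-to-treat population, taken at its word, creates speeds for patients who did not meet the condition. The analysis without missing data returns to the selected walkers.

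At stake is the reading of one stated secondary outcome. A real benefit on speed could be much understated, or a programme that only helps more patients to walk could look harmful to speed.

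**Working it through.** **Plan's own figure.** The only sample size is for S-TIS 2.0. A difference of 1.6, SD 4, two-sided alpha 0.05 and power 0.80 give 99 evaluable per group; 99 / 0.9 = 110, as stated. No SD, walking rate or effect is given for gait speed, so everything below is illustration under assumptions.

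**Setting the rules side by side**

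| Section 2.8 rule | Consequence for gait speed |
|---|---|
| Baseline to five-week change | No baseline value unless stepping is 6 at T0 |
| Intention-to-treat with imputation | Values filled in for patients below stepping 6, if these count as missing |
| Protocol followers, no missing data | Only patients at stepping 6 remain |

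**Case A: speed and reaching stepping 6 are one latent trait (correlation 1).** Let ability be L ~ N(0,1) in control and N(s,1) in experimental, with speed seen only when L > c. Write λ(x) = φ(x)/(1 − Φ(x)). The control mean among the measured is λ(c), the experimental mean is s + λ(c − s), and the observed difference is s + λ(c − s) − λ(c).

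With 30% of controls measured, c = 0.524 and λ(c) = 1.159. For s = 0.40 the experimental mean is 1.279, so the observed difference is 0.120 SD.

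| Controls measured | True shift | Observed difference | Attenuation |
|---|---|---|---|
| 20% | 0.40 SD | 0.099 SD | 75% |
| 30% | 0.25 SD | 0.071 SD | 71% |
| 30% | 0.40 SD | 0.120 SD | 70% |
| 50% | 0.40 SD | 0.164 SD | 59% |

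The difference shrinks but stays positive.

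**Case B: the programme brings more patients to stepping 6 but changes nobody's speed.** Assumptions: speed SD 0.25 m/s, correlation ρ between speed and walking ability of 0.3 to 0.8, a shift s of 0.25 or 0.50 SD in walking ability only, and 30%, 50% or 70% of controls reaching stepping 6. The true difference is zero. The walkers-only difference is 0.25 × ρ × [λ(c − s) − λ(c)].

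Worked case with 30% of controls, s = 0.50 and ρ = 0.8: 0.25 × 0.8 × (0.8135 − 1.159) = −0.069 m/s.

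| Controls at 6 | Shift | Experimental at 6 | Difference, ρ = 0.3 to 0.8 |
|---|---|---|---|
| 30% | 0.25 | 39% | −0.014 to −0.036 m/s |
| 30% | 0.50 | 49% | −0.026 to −0.069 m/s |
| 50% | 0.25 | 60% | −0.011 to −0.031 m/s |
| 50% | 0.50 | 69% | −0.022 to −0.058 m/s |
| 70% | 0.25 | 78% | −0.009 to −0.024 m/s |
| 70% | 0.50 | 85% | −0.016 to −0.043 m/s |

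The table comes from simulation with 4 million draws per arm; the formula agrees to within 0.001 m/s. With 99 evaluable per arm, a nominal 5% two-sided test among the measured rejects in about 5.6% to 35% of trials, although no patient's speed was changed.

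**How many values are at issue.** Of 99 evaluable per arm, 99 × (1 − 0.30) = 69 down to 99 × (1 − 0.70) = 30 controls would have no five-week speed. In the experimental group the number runs from 60 down to 15.

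**The case against.** The condition has an obvious practical reason: an unaided one-minute walk cannot be asked of someone who does not walk independently. That stands, and the point is not against the measurement but against the analysis attached to it.

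A programme that brings more patients to independent walking would not go unnoticed, because stepping is scored in everyone at all five assessments. That also stands. It confines the matter to one secondary outcome; the primary outcomes and the sample size are untouched.

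Some stronger readings are tempting and go too far:

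- *A programme that improves speed could show a loss.* Case A does not show that: a shift in the common trait gives attenuation only. A negative difference arises in case B, where more patients reach stepping 6 and speed itself does not change.
- *The plan will impute these speeds.* Section 2.8 does not say that a test not done by design is missing data. It could be treated as not applicable, and an unseen analysis plan could exempt it. Imputation is the literal reading, not a stated fact; the other reading leads back to the selected comparison.
- *Patients below stepping 6 cannot walk.* Section 2.7 ties a score of 6 to independent walking over 5 m. A lower score does not rule out walking with help, so a speed of 0 m/s is a convention, not an observation.
- *The plan would judge speed against a difference of 0.6 to 0.8 m/s.* That label in the Discussion is a wording error; no analysis, success rule or sample size uses it.

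The illustrations depend heavily on assumptions. With a weak correlation the distortion is small: −0.009 m/s and 5.6% rejection at the lowest.

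**Conclusion.** The point holds for the way gait speed is to be compared. Measurement is conditional on a post-randomisation primary outcome that treatment is designed to change, so a walkers-only comparison is not a randomised one, and the single rule in section 2.8 gives no valid alternative. The bias arises only if the programme changes who reaches stepping 6, which is what the trial hopes to show.

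Its size cannot be derived from the documents. The 59-75% attenuation rests on correlation 1, a 0.40 SD shift and 20-50% of controls measured. The spurious deficit of about 0.01 to 0.07 m/s rests on no effect on speed, an SD of 0.25 m/s, correlations of 0.3 to 0.8, shifts of 0.25 to 0.50 SD and 30-70% of controls at stepping 6. Confidence is high on the selection problem, and lower on its size and on what imputation would do. The matter should be corrected, but it affects one secondary outcome only.

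**What to change.** Keep the measurement condition as it is and change the analysis wording:

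1. Analyse gait speed in all intention-to-treat patients with a rank-based or ordinal model, giving the worst rank to every attended visit with BBA stepping below 6. Alternatively, specify a two-part analysis: the proportion reaching stepping 6, then speed among those measured.
2. Adjust for baseline BBA stepping, which every patient has, instead of requiring a baseline speed.
3. Impute only when the visit itself was missed, not when the test was not done because stepping was below 6.
4. Label the mean speed among measured patients as descriptive.
5. In the Discussion, describe 0.6 and 0.8 m/s as absolute speeds and stop calling them a minimally important difference.

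A worst rank is preferable to a fixed 0 m/s, because it needs no claim that a patient below stepping 6 does not walk at all. The cost is wording only, since the stepping scores are already collected. The price is a less familiar effect measure, and one that partly overlaps with the stepping outcome.
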